## Methods/design

### Study design, setting and patient population

This is a randomized, controlled, open-label, multicenter study comparing two strategies for the management of AKI occurring in patients in the initial phase of septic shock: namely initiation of RRT within 12 hr of the onset of AKI versus initiation of RRT after 48 to 60 hr in the failure stage of the RIFLE classification [23] (see details below in Study definitions), or at the onset of criteria requiring emergency RRT. The study will be conducted in 24 ICUs (15 university teaching hospitals and 9 general (non-academic) hospitals) in France. All patients admitted to the ICUs of participating centers will be screened for eligibility. The study sponsor is the University Hospital of Dijon, France, where data will be managed by the Centre for Clinical Investigation and Clinical Epidemiology (CIC-EC).

### Inclusion criteria

• Age >18 years.

• Patients in the first 48 hr of septic shock developing AKI with at least one criterion characteristic of the failure stage of the RIFLE classification (defined below under Study definitions).

• Informed consent provided by the patient (or person with decisional responsibility).

• Patients must have social security cover.

### Exclusion criteria

The following conditions will lead to ineligibility for study entry:

• Chronic RRT.

• Obstructive etiology for AKI.

• Need for emergency RRT before randomization (hyperkalemia >6.5 mmol/L, metabolic acidosis with pH < 7.15 or extravascular fluid overload refractory to diuretics with pulmonary edema).

• AKI that has already been treated by RRT in the ICU.

• Confirmed or suspected pregnancy (verified by serum [b-HCG] pregnancy test if necessary).

• Patient is moribund with expected death within 24 hr.

• Patients for whom survival to 28 days is unlikely due to an uncontrollable comorbidity (cardiac, pulmonary or hepatic end-stage disease; hepatorenal syndrome; poorly controlled cancer; severe post-anoxic encephalopathy; etc.).

• Patients with advance directives issued expressing the desire not to be resuscitated.

• Patient under tutorship, curatorship or judicial protection.

• Enrollment in any concomitant randomized trial with mortality as a primary outcome.

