#### Emergency renal replacement therapy

By protocol and to minimize the potential bias of clinician discretion on when to initiate emergency RRT, at least one of the following criteria must be fulfilled prior to initiation of emergency RRT:

1) hyperkalemia ([K^+^] ≥6.5 mmol/L) with characteristic electrocardiographic changes

2) metabolic acidosis (pH <7.15) defined as a base deficit > 5 mEq/L or HCO_3_^–^ < 18 mEq/L

3) pulmonary edema

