The presence of criteria for emergency dialysis could be a barrier to good compliance in our study. To avoid this problem, we decided to exclude from the study patients who fulfilled emergency RRT criteria at ICU admission before randomization, although this could actually be a selection bias by limiting the inclusion of the most seriously ill patients. On the other hand, emergency criteria after randomization pose no problem for the study, because RRT will be initiated immediately regardless of the randomization group. The data will then be analyzed by ITT but also per protocol.

Another situation that may arise is that patients in the delayed RRT group recover adequate kidney function before RRT is initiated, and are not on RRT at 48 hr, but subsequently renal function gradually alters and RRT is started later. These patients will still be included in the ITT analysis and considered as adverse events, but a subgroup analysis of these patients is planned, since they constitute a particularly serious population with a very high mortality and therefore, merit evaluation.

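### The emergency-RRT criteria that exclude patients before randomisation differ from those that trigger RRT afterwards, so a patient can be eligible while already meeting a trigger

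*Protocol article*

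**What the plan says.** Four places in the protocol article bear on this.

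- **Exclusion criteria.** A patient is ineligible for "Need for emergency RRT before randomization (hyperkalemia >6.5 mmol/L, metabolic acidosis with pH < 7.15" or "extravascular fluid overload refractory to diuretics with pulmonary edema". The potassium item carries no ECG condition.
- **Emergency renal replacement therapy.** At least one listed criterion has to be met before emergency RRT is started. The stated purpose is to limit bias from clinician discretion. The criteria are "hyperkalemia ([K^+^] ≥6.5 mmol/L) with characteristic electrocardiographic changes", "metabolic acidosis (pH <7.15) defined as a base deficit > 5 mEq/L" (or a low bicarbonate), and "3) pulmonary edema" with no further qualification.
- **Study intervention, Initiation of RRT.** Delayed-arm patients are watched for 48 hr after randomisation for the criteria in the second list. If one appears, RRT begins as soon as it can be arranged.
- **Discussion.** To protect compliance, "we decided to exclude from the study patients who fulfilled emergency RRT criteria at ICU admission before randomization". This sentence presumes that there is a single list.

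**The concern.** The exclusion is meant to keep out patients who would need RRT at once whichever arm they were assigned to. It does so only if it covers every state that triggers RRT after randomisation, and as printed it does not.

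What is at stake is the only thing that separates the arms, namely when RRT starts. A patient who enters already meeting a trigger could be dialysed promptly in the delayed arm as well as in the early arm. Such a patient contributes to the intention-to-treat comparison of 90-day mortality but carries little or no timing contrast.

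The potassium rule conflicts in the other direction. The same laboratory finding is labelled an emergency need before randomisation and is not one after it, with no reason given. Centres following the text would apply two different ideas of an emergency to the same patient on either side of randomisation.

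**Working it through.** **Step 1. The two lists side by side.**

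| Item | Excludes before randomisation | Triggers RRT after randomisation |
|---|---|---|
| Potassium | above 6.5 mmol/L | 6.5 mmol/L or above, and ECG changes |
| Metabolic acidosis | pH below 7.15 | pH below 7.15, with a base-deficit or bicarbonate definition added |
| Fluid / lungs | overload refractory to diuretics, and pulmonary edema | pulmonary edema |

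**Step 2. Each combination against both lists.**

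| State at entry | Excluded? | Trigger met? |
|---|---|---|
| K 6.4, with or without ECG changes | no | no |
| K 6.5, no ECG changes | no | no |
| K 6.5, ECG changes | **no** | **yes** |
| K 6.6, no ECG changes | **yes** | **no** |
| K 6.6, ECG changes | yes | yes |
| Pulmonary edema, not refractory | **no** | **yes** |
| Overload with pulmonary edema, refractory | yes | yes |

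Three rows disagree. Two describe eligible patients who already meet a trigger. The edema row is the one that matters, since the potassium row concerns a single value. The third describes an excluded patient whose value triggers nothing later. The pH threshold is the same in both lists.

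**Step 3. The plan's own sample size.** Inputs from Sample size calculation: 55% versus 45% mortality, two-sided alpha 0.05, power 80%, 5% non-evaluable. With mean proportion 0.50,

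n = [1.960·√(2·0.50·0.50) + 0.842·√(0.55·0.45 + 0.45·0.55)]² / 0.10² ≈ 391.3, or 392 per arm.

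With the continuity correction, n′ = (n/4)·[1 + √(1 + 4/(n·0.10))]² ≈ 411.0, or 412 per arm. Allowing for 5% non-evaluable, 412/0.95 = 433.7, or 434 per arm and 868 in total. That is close enough to the stated 864 to count as reproduced. The list conflict does not affect this figure.

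**Step 4. Illustration of dilution.** The documents give no frequency for the affected patients, so a fraction f is assumed. The assumptions are that these patients have no timing effect and that the planned 10-point effect applies to everyone else. The expected difference is then 10·(1 − f) points, which can be written as delayed-arm mortality of 0.55 − 0.10·f against 0.45. Evaluable patients per arm are 0.95 × 432 = 410.4, taken as 410. The test is Fisher's exact test, as planned for the primary comparison.

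| f (assumed) | Delayed vs early | Exact Fisher power |
|---|---|---|
| 0 | 55.0% vs 45% | 79.2% |
| 5% | 54.5% vs 45% | 74.8% |
| 10% | 54.0% vs 45% | 70.0% |

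The loss is 79.2 − 74.8 = 4.4 points at 5% and 79.2 − 70.0 = 9.2 points at 10%.

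**The case against.** **Emergency starts belong to the delayed strategy.** Study design, setting and patient population defines that arm as RRT after 48 to 60 hr or when an emergency criterion arises. Intention to treat compares those two strategies, and an emergency start complies with the protocol. This stands. A reader might infer that the Discussion is wrong to say that "emergency criteria after randomization pose no problem for the study". In context that sentence is about compliance, and the design supports it. The point here is narrower and concerns patients who meet a trigger before they are randomised, whom the Discussion says are kept out.

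**Immediate RRT is an inference.** The article speaks of criteria appearing or arising after randomisation, so edema already present at entry is not clearly covered. This is fair, and it is why the point says that such a patient could start soon, not that every one would. The ambiguity is itself a reason to reconcile the text.

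**A wide exclusion does not bias the comparison.** Excluding potassium above 6.5 without ECG changes happens before randomisation and affects both arms alike. This also stands. What remains is a conflict of wording over what counts as an emergency need.

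**An article condenses the full protocol.** This covers the lack of an operational definition of pulmonary edema, which may sit in the full protocol or the eligibility checklist, so that is not raised. It does not cover two lists that are both printed and disagree. Nor does the phrase about need for emergency RRT import the second list, because the exclusion criterion spells out its own terms in parentheses.

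**Reporting is already planned.** Secondary analyses, item 6, will describe the number and characteristics of delayed-arm patients who meet an emergency criterion. No further request is needed.

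**Conclusion.** The contradiction is in the text and does not depend on any assumption. The Discussion's statement that patients meeting the emergency criteria are excluded is not true of the lists as printed. Pulmonary edema that is not refractory to diuretics, and potassium of exactly 6.5 mmol/L with ECG changes, both pass the exclusion and meet a trigger. Potassium above 6.5 without ECG changes does the reverse.

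The size of the effect cannot be determined from the documents. The powers of about 75% and 70% rest wholly on assumed fractions of 5% and 10% and on no timing effect in those patients. A reader might infer that the trial is badly underpowered, for example by supposing that 20% or 30% of the delayed arm starts at once. The documents do not support that. They give no such frequency, and fractions of that kind would cover all emergency starts, including those arising after randomisation, which reconciling the lists would not remove.

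This should be fixed. It does not by itself threaten the validity of the primary analysis.

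**What to change.** The investigators should reconcile Exclusion criteria, Emergency renal replacement therapy and the Discussion in three steps:

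1. Word the criteria so that no patient who already meets a post-randomisation trigger is eligible, as the Discussion says is intended.
2. Either align the potassium and pulmonary edema wording between the two lists or state why they differ. One identical list is one way to do this, but not the only one.
3. Carry the result into the eligibility checklist mentioned under Description of study flow.

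Which threshold or qualifier is right is a clinical matter for the investigators, and none is proposed here.

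The cost is one amendment and a checklist edit. Trial status reports 200 patients included, so 864 − 200 = 664 of the planned total would still be recruited after that date. Eligibility would change slightly part-way through, in a direction that depends on the wording chosen: extending the exclusion to all pulmonary edema would admit fewer patients, while adding the ECG condition to the potassium exclusion would admit more. The date of the change should be recorded so that patients enrolled before and after it can be told apart.

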### Study definitions

#### Septic shock

Septic shock is defined according to current guidelines [24,25] as sepsis-induced hypotension persisting despite adequate fluid replacement, requiring the initiation of vasopressor therapy. The initial phase of septic shock is defined as the first 48 hr after the start of vasopressor therapy.

#### Sepsis

The operational definition of the clinical syndrome of sepsis will be confirmed or suspected infection, and at least two systemic inflammatory response syndrome criteria, i.e. any two of the following: temperature >38°C or <36°C; heart rate >90 beats/min; respiratory rate >20 breaths/min, PaCO_2_ < 32 mmHg or mechanically ventilated; white cell count >12,000 cells/mm^3^, <4,000 cells/mm^3^ or with >10% immature (band) forms.

#### Acute renal failure

AKI will be defined and classified according to the RIFLE criteria (risk of renal dysfunction, injury to the kidney, failure of kidney function, loss of kidney function and end-stage kidney disease) as outlined by the Acute Dialysis Quality Initiative (ADQI) Working Group [23]. In brief, the RIFLE criteria classify AKI into three categories of severity (risk, injury and failure) and two categories of clinical outcome (loss and end-stage kidney disease) based on relative changes to serum creatinine and urine output. The presence of AKI will be defined by the failure stage of the RIFLE classification, namely an abrupt (within 7 days) reduction in kidney function, characterized by a threefold increase in serum creatinine relative to baseline; an absolute value ≥354 μmol/L (accompanied by an acute increase ≥44.2 μmol/L); a reduction in urine output of ≤0.3 mL/kg/hr for ≥24 hr; or anuria for ≥12 hr. If pre-hospital baseline serum creatinine is unavailable, baseline serum creatinine is estimated based on back-calculation of the abbreviated Modification of Diet in Renal Disease (MDRD) as recommended by the ADQI [23].

### Treatment

#### Renal replacement therapy

RRT will include any form of extracorporeal RRT for patients with documented AKI. Given the lack of demonstrated superiority of continuous over intermittent techniques, and of convective over diffusive techniques [26,27], investigators at each center will be free to choose the extra-renal purification technique based on their usual practice (intermittent hemodialysis, intermittent sustained low-efficiency dialysis (SLED), continuous hemodialysis, continuous hemofiltration or continuous hemodiafiltration) and can move from one technique to another depending on the needs of the patient (typically the continuous technique in the acute phase, followed by intermittent techniques after stabilization).

Vascular access is obtained through a double lumen catheter with a minimum diameter of 12 French, preferably implanted in the superior vena cava via the jugular approach, and whose end is positioned 1 cm from the junction between the superior vena cava and the right atrium, or alternatively at the inferior vena cava by the femoral route. Catheter placement under ultrasound guidance is strongly recommended but not mandatory. Investigators must follow international guidelines on the management of AKI [28,29] to standardize practices and optimize metabolic control and hemodynamic stability during treatment.

For continuous techniques, investigators must provide treatment continuously for 24 hr with a change of membranes at least every 72 hr. To be certain of administering the recommended dialysis dose despite interruptions for changing filters or for additional procedures away from the ICU, investigators must regulate a minimum ultrafiltration (or dialysate) rate of 25 mL/kg/hr.

For intermittent techniques, the recommendations are to set a blood flow rate of 150 to 250 mL/min, a dialysate flow rate of 300 to 500 mL/min, a high concentration of sodium in the dialysate (150 mmol/L) and a low temperature of the dialysate (35°C). Treatment should be initiated with an isovolemic connection (simultaneous connection of two lines filled with saline). The length of sessions must be at least 4 hr and preferably 6 hr or more. The frequency of sessions should be at least once every 48 hr, or more often if investigators deem it necessary to achieve optimal metabolic control, a urea concentration <30 mmol/L or a stable salt and water balance. Investigators will be required to use biocompatible membranes.

Investigators can use systemic anticoagulation with unfractionated heparin or low molecular weight heparin, or alternatively, regional citrate anticoagulation.

#### Early renal replacement therapy

The operational definition of early RRT is the initiation of RRT immediately after the diagnosis of AKI. A maximum of 12 hr is allowed between the diagnosis of AKI and the actual initiation of RRT, given the time required for dialysis catheter placement and installation of equipment for RRT, and allowing for technical difficulties that may be encountered in clinical practice.

#### Delayed renal replacement therapy

The operational definition of delayed RRT is the initiation of RRT at least 48 hr after the diagnosis of AKI. A maximum margin of 12 hr (i.e. up to 60 hr) is allowed before actual initiation of RRT, justified by the same technical reasons mentioned above for the early RRT group.

#### Emergency renal replacement therapy

By protocol and to minimize the potential bias of clinician discretion on when to initiate emergency RRT, at least one of the following criteria must be fulfilled prior to initiation of emergency RRT:

1) hyperkalemia ([K^+^] ≥6.5 mmol/L) with characteristic electrocardiographic changes

2) metabolic acidosis (pH <7.15) defined as a base deficit > 5 mEq/L or HCO_3_^–^ < 18 mEq/L

3) pulmonary edema

#### Renal recovery

Renal recovery is defined as the return of spontaneous urine output ≥1,000 mL/24 hr (or ≥2,000 mL/24 hr with diuretics) for a minimum of 24 hr without RRT.

### Trial protocol

#### Description of study flow

Patients will be identified in the ICU through daily surveillance by the research coordinator or treating ICU physician. Each patient’s eligibility will be verified by use of a checklist that summarizes the inclusion and exclusion criteria (Figure 1). Septic shock is considered as confirmed once vasopressor therapy is initiated. For patients diagnosed with septic shock, AKI must appear within 48 hr for the patient to be eligible (in addition to the failure criteria).

**Figure 1 F1:**
[figure not shown]
**Flow chart of the study groups.** The timing of diagnosis, randomization and initiation of renal replacement therapy in the early and delayed groups, according to the method used to diagnosis acute kidney injury, are shown.

#### Sample size calculation

It has been shown that the mortality of septic shock patients who develop AKI is around 50%. Assuming an absolute reduction in mortality of 10% (55% mortality at 90 days in the delayed RRT group versus 45% in the early RRT group), 864 patients (432 per group) are required to ensure 80% power at a bilateral alpha risk of 0.05, assuming a rate of 5% non-evaluable cases.

The expected reduction of 10% in mortality was chosen as a clinically relevant difference by the study team. There are currently no data in the literature that could serve as a precedent for this, due to wide variations between existing studies in the types of patients included, the definitions of AKI used, and the definition of what constitutes early or late treatment. In light of the heterogeneous data available, a conservative estimate of a 10% reduction was retained as being clinically relevant.

#### Informed consent

When patients meet the inclusion criteria, and do not present any non-inclusion criteria, they are informed (orally, with supporting documentation in written format) about the study by the investigators, and invited to participate. If the patient is temporarily incapable of receiving the appropriate information or making an informed decision regarding consent to participate, they can still be included if informed consent is given by the patient’s surrogate or legal representative. If the patient subsequently regains the capacity to understand the study procedures and provide informed consent, their consent must be obtained. Patients can be included in emergency situations if their condition precludes consent and no legal representative or close relative is available to provide consent. In this case, the investigator notes and justifies in the patient’s medical record that the patient was temporarily unable to receive the study information and provide informed consent, and that no legal representative or close relative could be reached. Written consent must subsequently be obtained from the patient, as soon as their clinical status allows.

#### Randomization

Randomization is performed during the first 48 hr of septic shock after the development of at least one criterion defining the failure grade of the RIFLE classification. Randomization takes place after verification of the eligibility criteria, following an online request by the investigator using Tenalea® software (Formsvision BV, Abcoude, Netherlands). This allocation is based on a minimization technique taking into account the center, age, sequential organ failure assessment (SOFA) score, site and type of infection. Patients are randomly assigned to one of the two groups in a 1:1 ratio. Due to the nature of the study intervention, blinding is not possible. However, the CIC-EC (Dijon) will manage all the data and generate blinded reports for the Data Safety and Monitoring Board. The investigators at the participating sites will remain unaware of study group outcomes until the database is locked.

### Study intervention

#### Initiation of RRT

Patients randomized to the early RRT arm will immediately undergo dialysis catheter placement. A maximum of 12 hr is allowed between the diagnosis of AKI and the actual initiation of RRT; this allows for the time required for catheter placement and installation of the RRT equipment, as well as any technical difficulties that may be encountered in clinical practice.

Patients randomized to the delayed RRT group will be closely monitored for 48 hr after randomization to identify as soon as possible the appearance of criteria requiring emergency RRT as defined above. If any of these criteria occur, dialysis catheters are placed and the RRT will be initiated as soon as possible.

In the absence of the appearance of criteria requiring emergency RRT, patients randomized to the delayed RRT group will undergo insertion of the dialysis catheter and initiation of RRT at least 48 hr after the diagnosis of AKI, with a maximum margin of 12 hr allowed (i.e. up to 60 hr maximum), justified by the same technical reasons mentioned above for the early RRT group.

If a patient in the delayed RRT group recovers normal renal function (defined according to the criteria for recovery of renal function listed above) within the 48 hr after randomization, the investigator is free to choose the most suitable treatment and is therefore not obliged to dialyze the patient, but must, in this case, document the absence of RRT and the normalization of renal function.

